### Statistical Considerations

The statistical methods applied for this study are subject to GCP guidelines (Guidelines of the International Conference on Harmonisation (ICH) e.g.

• ICH E3: Structure and Contents of Clinical Study Reports,

• ICH E6: Good Clinical Practice (GCP). Consolidated Guideline,

• ICH E9: Note for Guidance on Statistical Principles in Clinical Trials) and will be performed in accordance with CESAR SOP 8 (Statistical Analysis/Biometry) in their versions valid at the date of the original study protocol.

### Study Hypothesis

The study is designed to demonstrate that a carbon ion boost in combination with postoperative photon radiotherapy can improve the progression-free survival rate after 3 years (PFS-3yR) by 20%. The benchmark for largest PFS-3yR which, if true, implies that the efficacy of study treatment is too low is assumed to be 50% according to literature data (4) with a comparable patient population (patients with atypical meningiomas Simpson grade 4 and 5 and without previous radiotherapy).

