## Abstract

**Background:**

Treatment standard for patients with atypical or anaplastic meningioma is neurosurgical resection. With this approach, local control ranges between 50% and 70%, depending on resection status. A series or smaller studies has shown that postoperative radiotherapy in this patient population can increase progression-free survival, which translates into increased overall survival. However, meningiomas are known to be radioresistant tumors, and radiation doses of 60 Gy or higher have been shown to be necessary for tumor control.

Carbon ions offer physical and biological characteristics. Due to their inverted dose profile and the high local dose deposition within the Bragg peak precise dose application and sparing of normal tissue is possible. Moreover, in comparison to photons, carbon ions offer an increased relative biological effectiveness (RBE), which can be calculated between 2 and 5 depending on the cell line as well as the endpoint analyzed.

First data obtained within the Phase I/II trial performed at GSI in Darmstadt on carbon ion radiotherapy for patients with high-risk meningiomas has shown safety, and treatment results are promising.

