**Discussion:**

Based on published data on the treatment of atypical meningiomas with carbon ions at GSI, the present study will evaluate this treatment concept in a larger patient population and will compare outcome to current standard photon treatment.

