**Non-radical**	
**Stage 3**	complete excision but insufficient dural coagulation or bone excision (non visible on MR, according to surgeon's opinion)
**Stage 4**	incomplete excision, macroscopic rest visible (on MRI)
**Stage 5**	biopsy only (visible on MRI)

Patients after non-radical resection (Simpson Grade 4 and 5) show significantly worse outcome than patients after radical neurosurgical resection [4]: In patients with non-bening meningiomas treated with surgery alone, local recurrence rates are 50% for subtotally excised, and 90% for completely resected patients at 3 years as reported in a large multi-center overview. Local recurrence has a major negative impact on survival.

Although meningiomas are classified as relatively radioresistant tumors, radiation therapy is the most effective adjuvant treatment available [5-8]. For non-benign meningiomas, a number of small and non- controlled series have reported superior outcome after postoperative radiotherapy as compared to surgery alone [6,9-13].

Novel radiotherapeutic modalities such as protons or carbon ion radiotherapy offer a promising treatment alternative. Radiation therapy using charged particles is characterized by distinct physical and biological characteristics. Charged particles provide the physical advantage of an inverted dose profile which enables steep dose gradients. Therefore, reduction of dose to normal tissue, and especially to organs at risk, can be achieved. Heavy charged particles, such as carbon ions, additionally offer an increased RBE. Thus, with particle therapy, dose escalation required for long-term control of atypical or malignant meningiomas is feasible while adhering to normal tissue tolerance constraints. New beam qualilties, such as carbon ion radiation therapy, offer a promising treatment alternative in malignant meningiomas. Carbon ion radiotherapy offers the physical characteristics as do protons, however, are characterized by a comparably higher RBE. For aggressive and radioresistant tumors auch as glioblastoma cell lines, RBE values between 2 and 5 have been reported depending on cell line and endpoint [14,15]. Clinically, it has been shown that carbon ion radiation therapy leads to significantly increased control rates in treatment-resistant tumors [16-18].

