### Inclusion criteria

Patients meeting all of the following criteria will be considered for admission to the trial:

- histologically confirmed atypical meningioma

- macroscopic tumor after biopsy or subtotal resection - Simpson Grade 4 or 5

- prior photon radiotherapy to the CTV_Photon _of 48-52 Gy

- beginning of study treatment no later than 12 weeks after surgery

- age ≥ 18 years of age

- Karnofsky Performance Score ≥60

- For women with childbearing potential, adequate contraception.

- Ability of subject to understand character and individual consequences of the clinical trial

- Written informed consent (must be available before enrolment in the trial)

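### The 50% null benchmark appears to be a surgery-alone figure, so rejecting H0 would support the photon-plus-boost regimen but would not show that the boost adds to photon radiotherapy

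*Protocol article*

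**What the plan says.** **The benchmark.** Protocol article, Study Hypothesis: the largest PFS-3yR that counts as too low "is assumed to be 50% according to literature data (4) with a comparable patient population". The section describes that population as "patients with atypical meningiomas Simpson grade 4 and 5 and without previous radiotherapy". Confirmatory Analysis tests H0: PFS-3yR ≤ 0.5 with a one-sided binomial test at 5%.

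**Where reference 4 appears in the Background.** After Table 1, the Background says that patients with Simpson grade 4 and 5 resections "show significantly worse outcome than patients after radical neurosurgical resection [4", citing reference 4. The same sentence continues after a colon: in patients "treated with surgery alone, local recurrence rates are 50% for subtotally excised, and 90% for completely resected patients at 3 years". The Abstract says of neurosurgical resection: "With this approach, local control ranges between 50% and 70%, depending on resection status".

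**What trial patients receive.** The Inclusion criteria require "prior photon radiotherapy to the CTV_Photon" of 48-52 Gy, and everyone then receives the carbon boost. Methods and Design describes one arm at one center.

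**What is claimed.** The Abstract, under Discussion, says the study "will compare outcome to current standard photon treatment". The Background closes by saying that the impact of the carbon boost will be evaluated. It also says that small uncontrolled series in non-benign meningioma "have reported superior outcome after postoperative radiotherapy as compared to surgery alone".

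**The concern.** In a single-arm trial the null value is the only comparator in the confirmatory test, so what that value represents decides what a rejection means. Here it appears to describe patients who had surgery and no radiotherapy, while all trial patients have photons as well as the boost. On the article's own account, postoperative radiotherapy improves on surgery alone. Photons without any boost could therefore lift the rate above 50% and produce a positive test.

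At stake is the conclusion. The 5% error rate protects the statement that the combined regimen exceeds 50%. It does not protect a statement that the boost improves on photon treatment, which is the comparison the Abstract announces.

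**Working it through.** **1. Where the 50% comes from.** Set the two sections side by side:

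| Feature | Study Hypothesis | Background, after Table 1 |
|---|---|---|
| Reference | 4 | 4 |
| Resection | Simpson 4 and 5 | Simpson 4 and 5; figure given for subtotal excision |
| Time point | 3 years | 3 years |
| Value | 50% progression-free | 50% local recurrence, i.e. 1 − 0.50 = 50% without local recurrence |
| Treatment | without previous radiotherapy | surgery alone |
| Histology | atypical | non-benign |

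Reference, grades, time point and value agree. No photon-only 3-year PFS for this population appears anywhere in the article.

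**2. Reproducing the plan's sample size.** Inputs from Sample Size Calculation: p0 = 0.50, p1 = 0.70, one-sided alpha 5%, power 80%. Let X be the number of patients progression-free at 3 years, X ~ Binomial(n, p). The smallest n with P(X ≥ r | 0.50) ≤ 0.05 and P(X ≥ r | 0.70) ≥ 0.80 is n = 37 with r = 24, that is, at most 37 − 24 = 13 events:

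- P(X ≥ 24 | n = 37, p = 0.50) = 0.0494, matching the stated actual alpha of 0.049.
- P(X ≥ 24 | n = 37, p = 0.70) = 0.807.

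The plan's 37 is confirmed. The text prints rejection when events are fewer than 13 (r = 25), which gives alpha 0.0235 and power 0.698. Both rules are carried below because the printed rule and the stated alpha disagree.

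**3. Chance of a positive test if the boost adds nothing.** The true PFS-3yR then equals the photon-only rate q, which the article does not give. For assumed q, the success probability is P(X ≥ r | n = 37, p = q):

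| Assumed photon-only PFS-3yR | At most 13 events | Fewer than 13 events (as printed) |
|---|---|---|
| 50% | 0.049 | 0.024 |
| 55% | 0.149 | 0.084 |
| 60% | 0.335 | 0.222 |
| 65% | 0.582 | 0.445 |
| 70% | 0.807 | 0.698 |

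The error rate for a claim about the boost is at or below 5% only if photons add essentially nothing to the 50%.

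**4. Endpoint behind the figure.** The Background's 50% is local recurrence. PFS as defined in the article also counts death from any cause, so surgery-alone PFS would be at or below 50%.

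**The case against.** **The source is inferred.** The Study Hypothesis section never says surgery alone. Its phrase about no previous radiotherapy resembles the trial's own exclusion of earlier brain radiotherapy, and could mean radiotherapy-naive at entry. The Background attributes its figures to a multi-center overview of non-benign tumors and reports local recurrence rather than PFS. What reference 4 reports cannot be checked here. This stands, and it is why the heading says the benchmark appears to be a surgery-alone figure. On the other reading, the plan still does not say how the reference patients were treated, and nothing supports 50% as a photon rate.

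**The true photon rate may be near 50%.** The Background says 60 Gy is not enough for lasting control in atypical and anaplastic tumors. Table 2 has a 16-patient proton-plus-photon series with 19% local control at 8 years for atypical tumors. Under a constant hazard that is 0.19^(3/8) = 0.54 at 3 years, where the success probability is 0.11 (0.06 under the printed rule). This is fair as a reason to include the low end of the range. It is not a benchmark: the series is tiny, not photon-only, and reports local control with no resection status.

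**The test answers its own question.** The intervention is defined as the boost in combination with photons. A single-arm phase II trial may test a combined regimen against a historical threshold, and failure to isolate one component is inherent in that design. This stands. The fault lies in the claim attached to the benchmark, not in the design type or the arithmetic.

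**Stronger readings that a reader might infer.** One is that the subtotal-resection benchmark should be 10%, because the Background gives complete resection the worse rate (90%) right after saying incomplete resection does worse. The documents do not support this. If the two figures are mislabelled control rates, the subtotal value remains 50%, and the Abstract's 50-70% local control after resection does not fit 10%. Another is that the local-recurrence/PFS mismatch makes the 50% too easy. Against surgery alone it works the other way: 50% would be a conservative reference.

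**Conclusion.** The point holds in limited form. The 50% null value appears to be the surgery-alone figure from the Background, and the article offers no support for it as a photon-radiotherapy rate. Rejecting H0 would show that photons plus boost exceed 50% at 3 years. It would not show that the boost adds to photons, and it does not deliver the promised comparison with standard photon treatment.

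The size depends on a photon-only rate that must be assumed. For 55% to 70%, a boost with no effect would still yield a positive test with probability 0.15 to 0.81 (at most 13 events) or 0.08 to 0.70 (printed rule). These figures assume 37 evaluable patients, each with a known 3-year status.

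It would go too far to say that the benchmark is proven to be surgery-alone, that the binomial test is invalid, or that 37 is miscalculated. The first rests on matching features across two sections; the other two are contradicted by the reproduction above.

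**What to change.** 1. In Study Hypothesis and Confirmatory Analysis, state what treatment the reference 4 patients received and whether the 50% is PFS or freedom from local recurrence. Add that rejecting H0 supports only the photon-plus-boost regimen against that 50% reference.
2. In the Abstract's Discussion, delete the comparison with standard photon treatment, or qualify it as an informal, non-confirmatory comparison with published series.
3. Correct the Background sentence with the 50% and 90% rates, which contradicts the statement just before it, and check it against its source.

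These are wording changes and leave the sample size as it is. The downside is a weaker claim.

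If the sponsor wants the test itself to speak to photon treatment, p0 would have to be re-derived from photon-irradiated Simpson 4 and 5 atypical meningioma on the PFS definition, and N recalculated. Holding p1 at 70%, a p0 of 55%, 60% or 65% needs 70, 143 or 545 evaluable patients for 80% power. Holding a 20-point gain instead needs 37, 36 or 31, at the price of a more ambitious target. Even then the comparison remains historical.

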### Sample Size Calculation

The sample size calculation is based on the analysis of the primary endpoint PFS-3yR, denoting the rate of progression-free survival after 3 years of follow-up. The trial is designed to detect an improvement by 20% in this primary endpoint. For sample size calculation, the following hypotheses will be made:

• p_0 _is the largest PFS-3yR which, if true, implies that the efficacy of the treatment is too low. In the present trial p_0 _has been taken as 50%.

• p_1 _is the lowest PFS-3yR which, if true, implies that the efficacy of the treatment is adequate. In the present trial p_1 _has been taken as 70%.

• α is the accepted probability of considering adequate efficacy of the treatment with a true PFS-3yR equal or lower to p_0_. In the present trial α has been taken as 5% (actual 0.049).

• β is the accepted probability of rejecting adequate efficacy of the treatment with a true PFS-3yR at least equal to p_1_. In the present trial α has been taken as 20% (actual 0.0193).

Using the one-sided binomial test with the given hypotheses, the study required 37 patients to decide whether the PFS-3yR is less than or equal to 0.5 or greater than or equal to 0.7. If the number of progressions or deaths is lower than 13, the hypothesis that PFS-3yR ≤ 0.5 is rejected with a target error rate of 0.05 and an actual error rate of 0.049. Sample size calculation was done using the software PASS 2008.

Allowing for approximately 10% non-evaluable patients primarily due to drop out, n = 40 patients will be recruited.

Assuming the distribution of PFS events is exponential, PFS-3yR = 0.5 resp. PFS-3yR = 0.7 is equivalent to a median PFS = 3 years resp. median PFS = 5.8 years.

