### Statistical Methods

#### Confirmatory Analysis

The primary aim and its corresponding endpoint are subject to a confirmatory statistical analysis. The primary aim is to evaluate efficacy of carbon ion boost in combination with postoperative photon radiotherapy in patients with atypical meningiomas Simpson grade 4 and 5 on progression-free survival rate after 3 years of follow-up (PFS-3yR). Formally,

H_0_: PFS-3yR ≤ 0.5 versus H_1_: PFS-3yR > 0.5.

PFS-3yR is statistically tested with a one-sided binominal test on the level α = 5%.

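### The achieved type II error is printed as 0.0193 under the symbol α; the exact value for the design is 0.193, so power is about 81%, not 98%

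*Protocol article*

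**What the plan says.** The Sample Size Calculation section of the protocol article lists four design quantities as bullets.

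- The null and alternative 3-year progression-free survival rates are 50% and 70%.
- The third bullet deals with the type I error: "In the present trial α has been taken as 5% (actual 0.049".
- The fourth bullet opens with the type II error: "β is the accepted probability of rejecting adequate efficacy of the treatment with a true PFS-3yR at least equal to p_1". Its next sentence reads "In the present trial α has been taken as 20% (actual 0.0193".

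The text after the bullets says that "the study required 37 patients to decide whether the PFS-3yR is less than or equal to 0.5 or greater than or equal to 0.7". It then rejects the null hypothesis when fewer than 13 progressions or deaths occur, with a target error rate of 0.05 and an actual rate of 0.049. Recruitment is set at 40 to allow for roughly 10% non-evaluable patients. The Confirmatory Analysis section repeats the test and its level: "PFS-3yR is statistically tested with a one-sided binominal test on the level α = 5". The article gives the achieved type II error nowhere else and never states the power directly.

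**The concern.** There are two faults in one sentence. The bullet defines β, but the value is assigned to α. Taken literally, the section therefore sets α at 5% in one bullet and at 20% in the next. The achieved value of 0.0193 is also out of line with its own 20% target. A one-stage binomial design of minimal size lands just under its target β, not at a tenth of it.

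The figure describes how the trial's only confirmatory test performs. As printed, the test would miss a true 70% rate about once in 52 trials (1/0.0193). At β = 0.193 it misses it about once in five (1/0.193 = 5.2). Someone weighing a negative result would be given far too favourable a picture of the test's ability to detect the targeted effect.

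**Working it through.** **Inputs** (all from Sample Size Calculation; the test is repeated in Confirmatory Analysis)

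- n = 37 evaluable patients
- p0 = 0.50, p1 = 0.70
- one-sided exact binomial test, target α = 0.05, target β = 0.20
- printed actual α = 0.049; printed actual β = 0.0193
- printed rule: reject when events are fewer than 13, that is, 12 or fewer

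**Formulas.** Let X be the number of patients progression-free at 3 years, and reject when X ≥ r, which is the same as at most n − r events.

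- α = P(X ≥ r | n, p0) = Σ from k = r to n of C(n,k) · p0^k · (1 − p0)^(n−k)
- β = P(X ≤ r − 1 | n, p1) = 1 − P(X ≥ r | n, p1)

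**Step 1: reproduce the plan's n and α.** For each n from 20 upward, take the smallest r with exact α ≤ 0.05 and look for the first n with power of at least 0.80. The answer is n = 37 with r = 24 (13 or fewer events):

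- α = P(X ≥ 24 | 37, 0.50) = 0.0494, which agrees with the printed 0.049.

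The sample size and the actual α therefore both reproduce, and the intended design is identified.

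**Step 2: β at the same cut-off.**

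- Power = P(X ≥ 24 | 37, 0.70) = 0.8071
- β = 1 − 0.8071 = 0.1929, or 0.193 to three decimals

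The printed 0.0193 has the same digits with an extra zero after the decimal point: 0.193 / 0.0193 = 10. It implies power of 1 − 0.0193 = 0.9807.

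**Step 3: could another reading give 0.0193?**

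| Reading | Rule | α | Power | β |
|---|---|---|---|---|
| n = 37, cut-off matching α = 0.049 | ≤ 13 events | 0.0494 | 0.8071 | 0.1929 |
| n = 37, rule as printed | ≤ 12 events | 0.0235 | 0.6983 | 0.3017 |
| n = 36 | ≤ 12 events | 0.0326 | 0.7365 | 0.2635 |
| n = 38 | ≤ 13 events | 0.0365 | 0.7745 | 0.2255 |
| n = 40, all recruited patients | ≤ 14 events | 0.0403 | 0.8075 | 0.1926 |

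The one-sided normal approximation at n = 37 gives power Φ((0.20·√37 − 1.645·0.50)/√0.21) = 0.805. With the variance under p1 in both places it gives 0.844, and the two-sided 5% version gives 0.697. None of these is near 0.981.

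**Step 4: what would 0.0193 require?** With p0 = 0.50, p1 = 0.70 and one-sided α ≤ 0.05, the first sample size with β ≤ 0.0193 is n = 82 (at least 49 progression-free, β = 0.0179). Alternatively, keeping n = 37 and 13 or fewer events, the true rate would have to lie between 78% (β = 0.0211) and 79% (β = 0.0142), not at 70%.

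**The case against.** The best counter-argument is that this is a misprint which the sentence itself largely exposes. The 20% target is printed a few words earlier and is right, 37 is the correct exact sample size, and 0.0193 is plainly 0.193 with a slipped decimal. The figure enters no other calculation. Rejection of the null depends on α alone, and α is fixed at 5% both in its own bullet and under Confirmatory Analysis, so nobody would run the test at 20%. The article states no power, so the 98% is the complement of the printed β rather than a claim by the authors. Nor is that complement the certainty with which a negative result excludes a 70% rate; the estimate and its confidence interval would speak to that.

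Most of this stands. The sample size, the test and its level are untouched, and the practical harm is limited to how the design and a negative result are read. The objection does not make the number right. It is the only achieved type II error given for the confirmatory test, nothing elsewhere in the article corrects it, and it is wrong by a factor of ten.

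A second objection is that 81% belongs to a cut-off of 13 or fewer events, while the article prints a rule of 12 or fewer. That is true. The cut-off is a separate inconsistency in the same section, and a more consequential one because it changes when the null is rejected. It does not rescue 0.0193, since the printed rule gives an even larger β of 0.302. It does mean that the corrected β has to be stated together with the cut-off it belongs to.

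**Conclusion.** The point holds. The sentence should refer to β, and the achieved value should be 0.193, which corresponds to 80.7% power instead of the implied 98.1%. This assumes 37 evaluable patients, an exact one-sided binomial test of 50% against 70%, and rejection at 13 or fewer events, the only cut-off at n = 37 that yields the article's own actual α of 0.049. If the printed rule of fewer than 13 events were applied instead, β would be 0.302 and power 69.8%, which misses the 20% target. The sample size of 37 and the recruitment target of 40 do not depend on the misprinted figure.

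**What to change.** In the fourth bullet of Sample Size Calculation, replace α by β and 0.0193 by 0.193. Add that power is 80.7% with rejection at 13 or fewer events (at least 24 progression-free) among 37 evaluable patients. Before issuing the correction, confirm the cut-off against the original sample size output and bring the sentence on the number of events into line with it, so that n, cut-off, α and β all describe one design: 37 patients, 13 or fewer events, 0.049 and 0.193.

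The correction itself costs one symbol and one figure. Aligning the cut-off is one further wording change in the same section. Neither affects recruitment, follow-up or the planned test.

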### Analysis Populations

#### Full Analysis Population

The full analysis set (FAS) according to intention to treat (ITT) consists of all patients included in the trial irrespective whether any protocol violation was present at the time of treatment start or during treatment under study conditions or whether the patient withdrew consent or was taken off-study any time after treatment start.

Not included are patients who withdraw informed consent before start of treatment or about whom it becomes known that major in/exclusion criteria were violated which would have excluded them from study treatment when known at start of treatment.

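### The printed rejection count (fewer than 13 events) is not the 5% binomial test at 37 to 40 patients, and even the correct count for 37 does not carry over to 40 or 36

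*Protocol article*

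**What the plan says.** All places are in the protocol article.

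- **Sample Size Calculation, decision rule.** For 37 patients, a null 3-year PFS rate of 50% and an alternative of 70%, the rule is "If the number of progressions or deaths is lower than 13, the hypothesis that PFS-3yR ≤ 0.5 is rejected". The type I error is given as "In the present trial α has been taken as 5% (actual 0.049", the figure referring to this rule. The type II error is given as "In the present trial α has been taken as 20% (actual 0.0193", where the symbol should be β.
- **Sample Size Calculation, recruitment.** After an allowance of roughly 10% for non-evaluable patients, "n = 40 patients will be recruited".
- **Full Analysis Population.** Patients stay in this set regardless of protocol violations "or whether the patient withdrew consent or was taken off-study any time after treatment start". Those who withdraw consent before treatment, or prove to have violated major eligibility criteria, are left out.
- **Confirmatory Analysis.** "PFS-3yR is statistically tested with a one-sided binominal test on the level α = 5" percent. This section gives no event count and does not name the analysis set.

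No section gives a cut-off for a number other than 37, or says whether the count or the test decides if they differ.

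**The concern.** A binomial cut-off belongs to one sample size. The article prints one count, ties it to 37 patients, recruits 40, and leaves the analysed number open. Two questions follow. Does the printed count match the stated error at 37? Does any single count remain the 5% test at the other numbers that could be analysed?

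If the answer to either is no, the article contains two rules for the primary conclusion that can give opposite verdicts on the same data. A count that is too strict costs power in a 40-patient trial. A count that is too lenient breaks the stated 5% level.

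**Working it through.** **Inputs**, all from Sample Size Calculation: event probability 1 − 0.5 = 0.5 under the null and 1 − 0.7 = 0.3 under the alternative; one-sided level 0.05; target power 80%; 37 patients required, 40 recruited. Every analysed patient is taken to have a known 3-year status.

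**Formulas.** If H0 is rejected at c or fewer events among n patients:

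- level(n, c) = Σ_{k=0..c} C(n,k) · 0.5^n
- power(n, c) = Σ_{k=0..c} C(n,k) · 0.3^k · 0.7^(n−k)

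The exact 5% test uses the largest c with level(n, c) ≤ 0.05.

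**Step 1: reproduce the plan's design.** Scanning n = 20 to 44, the smallest n with exact power of at least 80% is 37, as stated. Its cut-off is c = 13: level 0.0494, power 0.8071, β = 0.1929. The stated 0.049 therefore belongs to at most 13 events. The printed 0.0193 appears to be 0.193 with a misplaced decimal.

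**Step 2: the printed count.** Lower than 13 means c = 12. At n = 37 this gives level 0.0235 and power 0.6983, so the printed rule already departs from its stated error at the design number.

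**Step 3: both counts against the exact test** (level / power):

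| n | Printed, at most 12 | Corrected, at most 13 | Exact 5% test |
|---|---|---|---|
| 35 | 0.0448 / 77.3% | 0.0877 / 86.5% | at most 12: 0.0448 / 77.3% |
| 36 | 0.0326 / 73.7% | 0.0662 / 83.7% | at most 12: 0.0326 / 73.7% |
| 37 | 0.0235 / 69.8% | 0.0494 / 80.7% | at most 13: 0.0494 / 80.7% |
| 38 | 0.0168 / 65.9% | 0.0365 / 77.4% | at most 13: 0.0365 / 77.4% |
| 39 | 0.0119 / 61.8% | 0.0266 / 74.0% | at most 13: 0.0266 / 74.0% |
| 40 | 0.0083 / 57.7% | 0.0192 / 70.3% | at most 14: 0.0403 / 80.7% |

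At n = 39, 14 events would have level 0.0541, so 13 is the correct limit there.

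**Step 4: split the loss at n = 40.**

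- Total: 0.8074 − 0.5772 = 0.230.
- From the off-by-one: 0.7032 − 0.5772 = 0.126.
- From holding the n = 37 count fixed: 0.8074 − 0.7032 = 0.104.

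The same differences give the chance of conflicting verdicts at a true 3-year PFS of 70%. As printed, the count and the test disagree at 13 or 14 events in 40, about 23% of trials. With the count corrected, they disagree only at exactly 14 events, about 10%.

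**Step 5: below 37.** The allowance of about 10% gives 40 × 0.9 = 36. There the corrected count of 13 has level 0.0662, above 5%. The printed count of 12 happens to be the exact test at 35 and 36, and exceeds 5% only from n = 34 down (0.0607 at 34, 0.0814 at 33).

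**The case against.** The strongest reply is that there is only one analysis rule. The count stands under Sample Size Calculation, directly after the requirement of 37 patients, and carries an error rate specific to that number. It can be read as a description of the design, with Confirmatory Analysis supplying a test that adapts to any n. Cut-offs by realised n are also often left to an analysis plan. This has weight, and it is why the remedy is a clarification and not a redesign. It does not dispose of the point: the count is worded as a rejection rule, no section ranks it below the test, and it is wrong even for 37.

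Three stronger readings are tempting, and the document does not support them.

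- **That a fixed count from 37 patients fails throughout 38 to 40.** The printed count does, but it is not the cut-off for 37. The true one, at most 13, is the exact 5% test at 38 and 39. Power below 80% there comes from the discreteness of the binomial, and the exact test has the same power.
- **That all 23 points lost at 40 come from recruiting beyond 37.** About 13 come from the off-by-one and about 10 from the fixed count.
- **That intention to treat fixes the analysed number at 40.** The full analysis set has exclusions, some non-evaluable patients are expected, and Confirmatory Analysis names no set. Forty is possible, not assured.

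The printed rule is also conservative at 36 to 40. Its level passes 5% only at n = 34 or fewer, that is, with at least 6 of 40 (15%) lost, beyond the stated allowance.

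**Conclusion.** The point stands in two parts.

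First, the printed threshold is wrong as written. At 37 patients it has level 0.0235 and power 69.8%, not the stated 0.049 and the intended 80%. Across 37 to 40 patients it is stricter than the prescribed 5% test, and the power loss grows from about 11 points (80.7% − 69.8%) at 37 to 23 points at 40.

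Second, correcting the count to at most 13 does not by itself settle the matter. One fixed count would still be too strict at 40 (level 0.019, power 70.3% against 80.7%) and too lenient at 36 (level 0.066), the number that the 10% allowance implies.

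These figures rest on the article's own rates of 50% and 70%, on complete 3-year status in those analysed, and on an analysed number that the article does not fix. The change should be made, because it concerns the threshold for the primary conclusion.

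**What to change.** In Sample Size Calculation:

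1. Correct the count for 37 patients to at most 13 progressions or deaths (lower than 14), and label it the design value for 37 evaluable patients. Keeping the present count as an illustration would leave the error in place.
2. Add a sentence such as: H0 is rejected if the exact one-sided binomial p-value, computed for the number of patients in the primary analysis set, is at most 0.05. Name that set in Confirmatory Analysis.
3. Add the cut-offs: at most 12 events for n = 35–36, at most 13 for n = 37–39, at most 14 for n = 40.
4. In the same edit, relabel the second error rate as β and correct its actual value to 0.193.

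The cost is a sentence, a three-row table and two small corrections. No patients, visits or data are added. The wording should be settled before the primary outcome is examined, so that the choice between count and test cannot depend on the result.

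### The printed cut-off of fewer than 13 events among 37 patients does not have the stated error rate of 0.049, which belongs to 13 or fewer

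*Protocol article*

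**What the plan says.** Everything needed stands in two sections of the protocol article.

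**Sample Size Calculation.** The null and alternative PFS-3yR are 50% and 70%. The error rates are given as "In the present trial α has been taken as 5% (actual 0.049") and, in the bullet that defines β, as "In the present trial α has been taken as 20% (actual 0.0193"). The number of evaluable patients follows: "Using the one-sided binomial test with the given hypotheses, the study required 37 patients". The decision rule is "If the number of progressions or deaths is lower than 13, the hypothesis that PFS-3yR ≤ 0.5 is rejected", and the same sentence continues "with a target error rate of 0.05 and an actual error rate of 0.049". Recruitment is set at 40 to allow for about 10% non-evaluable patients.

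**Confirmatory Analysis.** H0: PFS-3yR ≤ 0.5 is set against H1: PFS-3yR > 0.5, and "PFS-3yR is statistically tested with a one-sided binominal test on the level α = 5"%. No event cut-off is given there.

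**The concern.** The rule and the error rate in one sentence appear to describe two different tests. Fewer than 13 events means 12 or fewer, whereas an error rate just under 5% with 37 patients is what one would expect from a boundary one event higher.

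PFS-3yR is the only endpoint tested confirmatorily, and this is the only numerical boundary in the document. If exactly 13 patients progress or die, the Sample Size Calculation section says not to reject H0, while the 5% test under Confirmatory Analysis rejects it. Settling that conflict after the count is known would be a post hoc choice of the primary result.

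**Working it through.** **Inputs**, all from Sample Size Calculation: n = 37, p0 = 0.50, p1 = 0.70, one-sided α = 0.05, β = 0.20.

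Let X be the number of progressions or deaths within 3 years among n patients, and let the rule reject H0 if X ≤ c. The event probability is 1 − PFS-3yR, that is 0.5 under p0 and 0.3 under p1. Then

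- α(c) = Σ (x = 0 to c) C(37, x) · 0.5^37
- power(c) = Σ (x = 0 to c) C(37, x) · 0.3^x · 0.7^(37−x)
- β(c) = 1 − power(c)

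**Step 1: reproduce the plan's own figures.** A search over n for exact α ≤ 0.05 and power ≥ 0.80 gives n = 37 as the smallest, with at least 24 patients progression-free, which is at most 13 events. There α = 0.0494, the printed 0.049. So the sample size and the error rate both reproduce, with c = 13.

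**Step 2: evaluate the printed rule.** Fewer than 13 events is c = 12, or at least 25 of 37 progression-free.

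| Rule at n = 37 | α | Power at 0.70 | β |
|---|---|---|---|
| At most 12 events (as printed) | 0.0235 | 0.698 | 0.302 |
| At most 13 events | 0.0494 | 0.807 | 0.193 |
| At most 14 events | 0.0939 | 0.887 | 0.113 |

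The difference in power is 0.8071 − 0.6983 = 0.1088. This is also the probability of exactly 13 events when the true PFS-3yR is 0.70.

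**Step 3: could another n rescue the printed rule?** With at most 12 events, α is 0.0448, 0.0326, 0.0235, 0.0168, 0.0119 and 0.0083 for n = 35, 36, 37, 38, 39 and 40. None is 0.049.

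**Step 4: compare with Confirmatory Analysis.** At 13 events of 37 the one-sided exact p-value is P(X ≤ 13 | 0.5) = 0.0494 < 0.05, so that test rejects. At 12 events both sections reject. At 14 the p-value is 0.0939 and neither does. The two sections differ at exactly one outcome.

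**Step 5: the printed actual β.** The value 0.0193 fits neither rule: β is 0.302 with at most 12 events and 0.193 with at most 13. It has the digits of 0.193 with the decimal point one place too far left. The same bullet names α where it defines β.

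**Step 6: what happens if the analysed number is not 37.** A fixed cut-off of 13 would be wrong for other n: α is 0.088 at n = 35, 0.066 at n = 36, and 0.019 (power 0.703) at n = 40. The largest cut-offs that keep exact α ≤ 0.05 are:

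| n | Reject if events at most | α | Power at 0.70 |
|---|---|---|---|
| 35 | 12 | 0.0448 | 0.773 |
| 36 | 12 | 0.0326 | 0.737 |
| 37 | 13 | 0.0494 | 0.807 |
| 38 | 13 | 0.0365 | 0.774 |
| 39 | 13 | 0.0266 | 0.740 |
| 40 | 14 | 0.0403 | 0.807 |

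**The case against.** The strongest reply is that the sentence under Sample Size Calculation only illustrates the design. The analysis itself is specified under Confirmatory Analysis as a one-sided 5% binomial test without a cut-off. That test is valid, rejects at 13 of 37 events, and has power 0.807 at n = 37. On this view nothing is lost, and the slip is in the safe direction in any case.

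Much of this stands. A reader might infer that the misprinted cut-off is the trial's only confirmatory decision rule, so that 13 events would certainly be declared a failure. The document does not support that, because it specifies the 5% test separately and does not say which section prevails. A reader might also infer that the trial is underpowered or that 37 is the wrong number. Neither follows: 37 is the smallest adequate number for the stated design, and the power loss arises only if the printed cut-off is applied. Nor is there any inflation of type I error, since 0.0235 is below 5%. Finally, the protocol does not print a power of 80%; that figure follows from its β of 20%.

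What the reply does not remove is the contradiction. The sentence is an explicit rejection rule paired with an error rate that it does not have, and it gives the opposite answer to the 5% test at 13 of 37 events.

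**Conclusion.** The point holds as an off-by-one error in the printed cut-off. Taken literally, the rule has α 0.0235 and power 0.698 instead of 0.0494 and 0.807. That is a loss of about 11 percentage points of power, and its β of 0.302 misses the stated 20%. The sections conflict only at 13 of 37 events, which has probability 0.109 if the true PFS-3yR is 0.70, or about one trial in nine under the alternative. The error is conservative and leaves the sample size unaffected. It should still be corrected, because the boundary of the primary test must be unambiguous before the results are known.

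These figures assume that exactly 37 patients are analysed, each with known 3-year status, and that the test is the exact binomial. That 13 or fewer was the intended boundary is an inference, but three printed items agree with it: the error rate of 0.049, the sample size of 37, and the digits of the actual β. Reading 0.0193 as a misplaced decimal for 0.193 is likewise an inference.

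**What to change.** In Sample Size Calculation:

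1. Change the cut-off to 13 or fewer (lower than 14) progressions or deaths among 37 patients, with α 0.049 and β 0.193 (power 0.807).
2. In the bullet that defines β, replace the symbol α by β and the actual value 0.0193 by 0.193.
3. State that the exact one-sided 5% binomial test under Confirmatory Analysis governs, and that the cut-off is recomputed if the analysed number differs from 37. At n = 40 it is at most 14 events (α 0.040, power 0.807); at n = 35 or 36 it is at most 12.

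The third item is needed because 40 patients are recruited. A cut-off of 13 carried over to 35 or 36 analysed patients would exceed the 5% level and turn a conservative slip into an anti-conservative one.

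The cost is a few words and one added sentence, with no extra patients and no change to the test.
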